**Methods:**

A two-arm cluster randomized controlled trial will be conducted in the Foumban Health District and Galim Health District. The intervention and control arms will each comprise 5 clusters with 121 child–caregiver pairs. Participants in the intervention arm will be organized into 5 caregivers’ peer-support platforms. A total of 12 educational sessions will be assigned to the intervention group by trained female Mbororo nutrition volunteers (n=6) and community health workers (n=6). The control arm will receive routine facility-based nutrition education. Data will be collected at 3-month and 6-month follow-up. Both descriptive statistics and multivariate logistic models will be used to estimate the effect of culturally tailored community-based nutrition education intervention (independent variable) on outcome variables (caregivers’ knowledge, attitude, and practice), child growth (weight, height/length, weight for age), and morbidity status (diarrhea, cough, and fever) between both arms. Data assessors will be blinded to the group allocation. Ethical approval (reference no. 2019/1002-07/UB/SG/IRB/FHS) was obtained from the Faculty of Health Sciences Institutional Review Board at the University of Buea.

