### Sample Size Determination

The following formula for comparing 2 groups [17] was used for the calculation of the minimum sample size (n):

 where *z*_α/2_ = *z*_0.15/2_ = 1.44 (from *z* score table), Zβ/2 = z_0.15/2_ = 0.75 (from *z* score table at 75%), P_1_= 0.32, P_2_ = 0.22, P_1_–P_2_ = pooled prevalence (prevalence in intervention group [P1] + prevalence in control group [P2]/2):

Considering the 10% nonresponse rate, the sample size (n) was adjusted to 242.

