## Results

From the preintervention study undertaken from August 2019 to September 2019, baseline data were collected and partially analyzed to inform the design and implementation of the intervention study. In February 2020, 10 Mbororo communities with 242 child–caregiver pairs were selected for the trial, while 6 CNVs and 6 CHWs were selected and trained to lead the trial. Data collection and analysis are ongoing, and results are not available for this manuscript.

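### The printed sample-size inputs imply roughly 388 to 420 pairs in total under standard two-proportion formulas, not the 242 (121 per arm) that the trial uses

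*Protocol article*

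**What the plan says.** Sample Size Determination in the protocol article introduces the calculation thus: "The following formula for comparing 2 groups [17] was used for the calculation of the minimum sample size (n". It sets the significance term at z = 1.44, for a two-sided level of 0.15. The power term is "Zβ/2 = z_0.15/2_ = 0.75 (from *z* score table at 75"%. The rates are "P_1_= 0.32, P_2_ = 0.22". It then equates P1 − P2 with the "pooled prevalence (prevalence in intervention group [P1] + prevalence in control group [P2]/2". The result is: "Considering the 10% nonresponse rate, the sample size (n) was adjusted to 242".

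Other sections show that 242 is the total over both arms. The Abstract states: "The intervention and control arms will each comprise 5 clusters with 121 child–caregiver pairs". The Results section says that "10 Mbororo communities with 242 child–caregiver pairs were selected for the trial", and Step 2 of the intervention puts 121 caregivers in the intervention arm.

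**The concern.** A two-group formula of the usual kind returns the number needed in each group. With the printed inputs that number is well above 121, so the plan's own assumptions do not support the figure it calls the minimum. The section is the only justification given for the size of the trial. A reader would take it that 242 pairs deliver about 75% power for a ten-point difference at the 15% level, and they do not. A null result on such a comparison could then be over-read as evidence of no effect.

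The labels add to the difficulty. P1 − P2 is a difference, not a pooled prevalence. The second z value carries three descriptions that do not agree.

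**Working it through.** **Inputs** (all from Sample Size Determination): z for significance 1.44; z for power 0.75, also labelled as 75%; P1 = 0.32; P2 = 0.22; nonresponse 10%. From these, P1 − P2 = 0.10 and the pooled prevalence is (0.32 + 0.22)/2 = 0.27.

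**The plan's figure.** 242/1.1 = 220 and 242 × 0.9 = 217.8. The total before the allowance would therefore be about 218 to 220, that is 109 to 110 per arm.

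**Power term.** A z of 0.75 corresponds to 77.3% power; exactly 75% power needs z = 0.674. The third label, z at 0.15/2, has just been given as 1.44. Both 0.75 and 0.674 are carried through below.

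**Per group with z = 0.75.** (1.44 + 0.75)² = 4.796.
- Pooled variance: 4.796 × 2 × 0.27 × 0.73 / 0.10² = 189.1
- Unpooled variance: 4.796 × (0.32 × 0.68 + 0.22 × 0.78) / 0.10² = 4.796 × 0.3892 / 0.01 = 186.7
- Mixed form (pooled under the null, unpooled under the alternative): 188.2

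The pooled form gives 2 × 189.1 = 378.1 in total. With the allowance this is 378.1 × 1.1 = 415.9 or 378.1/0.9 = 420.1, so 416 to 420, or 208 to 210 per arm.

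**Per group with z = 0.674.** (1.44 + 0.674)² = 4.469. The pooled form gives 4.469 × 0.3942 / 0.01 = 176.2, or 352.3 in total. That becomes 388 (× 1.1) or 392 (/0.9). The unpooled form is slightly lower: 4.469 × 0.3892 / 0.01 = 173.9 per group, or 2 × 173.9 × 1.1 = 383 in total.

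**Misreadings with the printed z values.**
- Treating 189.1 as the two-arm total gives 208 to 210 after the allowance, not 242.
- Reading the bracket literally, 0.32 + 0.22/2 = 0.43. This gives 4.796 × 2 × 0.43 × 0.57 / 0.01 = 235.1 before the allowance and 258.6 after it (× 1.1), not 242.
- A continuity correction raises the per-group figure to 206 to 209 before the allowance, further from 121.

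**Power with the actual size.** Power = Φ[(0.10 − z × √(0.3942/n)) / √(0.3892/n)], with z = 1.44.
- n = 121: (0.10 − 1.44 × 0.05708)/0.05671 = 0.314, so 62%
- n = 109 (121 less 10%): (0.10 − 1.44 × 0.06014)/0.05975 = 0.224, so 59%

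These figures treat caregivers as independent. Any positive correlation within the 10 communities would lower them.

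**The case against.** **The equation is not visible.** The displayed formula, and possibly a worked line after the definitions, are absent from the text available, and so is the cited source. It would be too strong to say that 242 cannot be obtained by any formula. This stands, and the claim is limited to the standard two-proportion forms. Those forms differ by less than 3 per group for a given power term, so the choice among them does not explain the gap. An inflation for clustering would raise the requirement, not lower it.

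**The cause.** A reader might infer that a per-group figure was used as the two-arm total. Two reconstructions point that way:
- prevalence 0.43 and z = 0.674 give 219.1, rounded up to 220, and 220 × 1.1 = 242;
- prevalence 0.27 and 85% power (z = 1.036) give 241.7 per group.

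Both replace the printed z of 0.75, and the second reaches 242 before the nonresponse allowance, contrary to the text. A third route fits as well and implies a different slip. Without the factor of 2, (1.44 + 0.674)² × 0.43 × 0.57 / 0.01 = 109.5, so 110 per group; 110 × 1.1 = 121 per arm and 242 in total. The documents do not decide between these, and no cause should be asserted.

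**The outcome.** A reader might also infer that the primary analysis has only 62% power. The documents do not support that. Table 1 makes the primary outcomes continuous change scores compared by t test, whereas the sample-size section uses two proportions for an outcome it does not name.

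**Minor points.** The misplaced bracket around the average may be only typographical. Multiplying by 1.1 rather than dividing by 0.9 is a convention, worth 416 against 420. Neither affects the conclusion.

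**Conclusion.** The sample-size statement is wrong as written. Under standard two-proportion formulas its printed inputs call for about 176 to 189 per group, or roughly 388 to 420 in total with 10% nonresponse (383 at the lowest, with unpooled variance and exactly 75% power). The trial has 242. On the pooled calculation, 121 per arm is about 58% of the 208 to 210 per arm needed with z = 0.75 (121/210 = 0.576; 121/208 = 0.582), and about 62% of the need at exactly 75% power (121/194 = 0.624; 121/196 = 0.617). For 32% versus 22% at the two-sided 15% level, power is about 62%, or 59% after 10% loss, instead of 75% to 77%.

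This rests on a standard per-group formula, 1:1 allocation and independent caregivers. Confidence is high for the mismatch and low for any account of how 242 arose.

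**What to change.** Rewrite the Sample Size Determination paragraph:
- Define the pooled prevalence as (P1 + P2)/2 = 0.27 and the difference P1 − P2 as 0.10.
- Give the power term one consistent value: z = 0.75 with 77% power, or z = 0.674 with 75%.
- Say that the formula yields n per group.
- Replace the claim that 242 is the minimum with the power that the fixed 121 per arm provides: about 62% for 32% versus 22% at the two-sided 15% level, and 59% after 10% loss, before any allowance for clustering. State that this refers to the binary comparison.

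The communities and pairs were selected in February 2020, so enrolment stays as it is. The cost is one rewritten paragraph and a less favourable power figure.

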### Sampling Strategy for the Trial

A multistage sampling approach, using probability and nonprobability sampling methods, was used to select the study sites and population as illustrated in Figure 2. In the first stage, Galim Health District and Foumban Health District were selected randomly by lottery method from the 7 health districts with the highest Mbororo populations. In the second stage, 7 health areas were purposively selected, and a list of Mbororo communities (n=23) was established.

**Figure 2 figure2:**
[figure not shown]
Flow chart of multistage sampling strategy for the intervention.

### Intervention

Our Nu-WASH model comprises nutrition, and water, sanitation, and hygiene components. The nutrition component includes the following: complementary feeding, which involves the nutrition needs for young children; benefits of continuous breastfeeding for up to 24 months of child age; nutritional value of locally available plant-based and animal-based food items; dietary diversity (nutrient-rich homemade recipes); benefits and challenges of adequate complementary feeding practices; and susceptibility to, and severity of, child undernutrition. The WASH component, aimed at improving caregivers’ WASH knowledge and practices, will include the following: WASH-related childhood diseases, including causes, susceptibility, and severity; water quality, including point-of-use household drinking water treatment (boiling and filtration), and safe storage; environmental sanitation, including safe collection of child feces; personal hygiene, including proper hand washing with soap before food preparation, before child feeding, after using the toilet, after disposing of garbage, and after cleaning the baby’s feces; food hygiene (preparation, covering, serving, and heating); and the perceived barriers and benefits of food hygiene.

### Intervention Development

To improve on the abilities of caregivers to prevent child malnutrition, Nu-WASH will be implemented and evaluated. The target for behavior change will be caregivers assigned to the intervention arm. As illustrated in Figure 3, the intervention will be delivered through 6 logical steps: baseline data collection; the formation of caregivers’ peer support groups (CPGs); the selection and training of female community nutrition volunteers (CNVs) and community health workers (CHWs); health education for caregivers through CPGs; monitoring and evaluation; and midline and postintervention data collection and analysis.

**Figure 3 figure3:**
[figure not shown]
Summary of treatment given in the intervention and control arms. CHW: community health workers; CNV: community nutrition volunteers; Nu-WASH; nutrition, water, sanitation, and hygiene.

#### Step 1: Baseline Data Collection

A formative study was conducted from August 2019 to September in 2019 to understand the local contextual factors and to inform the experimental design. A total of 10 Mbororo communities, comprising 242 mothers/caregivers and their children (aged 3–59 months), were selected for the intervention study. Baseline data on the household, caregivers, and child variables; caregivers’ nutrition-related KAP; and child anthropometric and morbidity status data were collected.

#### Step 2: Formation of CPGs

Caregivers in the intervention arm (n=121) were organized into 5 peer-support groups of 20 to 30 members. Each group per cluster will serve as the platform for group sessions and for interactions to enhance learning.

#### Step 3: Selection and Training of the CNVs and CHWs

Each participating community designated 1 Mbororo female (15 years and older) for training as a CNV. Selected CNVs and existing CHWs in the health areas were trained to lead the nutrition education and act as resource persons for nutrition information within their communities.

#### Step 4: Nutrition Education for CPGs

The CPGs in the intervention arm will be exposed to Nu-WASH and routine nutrition education offered during visits to the health care facilities in the study area. Two facilitators (1 CNV and 1 CHW) will be assigned to each CPG of the intervention arm. The intervention delivery strategy will involve group sessions and individual counseling. Each CPG will be exposed to 12 sessions: 1 session every fortnight for 6 months, each lasting for 90 to 120 minutes. A participatory and interactive delivery strategy will include lectures, discussions, question-and-answer sessions, and demonstrations. Participatory cooking demonstrations using selected combinations of food items from 7 food groups will be aimed at improving self-efficacy of preparing nutrient-rich diets. Posters showing various food groups with educational messages on nutrition (cues to action) will be provided to reinforce behavior change. Caregivers facing challenges will be given personalized counseling sessions by the CNVs and CHWs. Nutrition and WASH-related perceived barriers and benefits will be explored and discussed during the training. The control group will receive routine health facility–based nutrition and counseling offered by health care providers in the study area.

#### Step 5: Monitoring and Evaluation

CNVs and CHWs will visit households once monthly to monitor compliance and encourage proper child-feeding practices, treatment, and safe storage of drinking water. Data relevant to the study will be collected during each visit with the use of structured observation forms.

#### Step 6: Midline and Endline Data Collection and Analysis

Data will be collected from both the intervention and control arm at 3-months and 6-month follow-up with the same data collection tools, methods, and procedures as those used at baseline.

### Study Objectives

#### Primary Objective

The primary objective will be to investigate the impact of a Nu-WASH versus facility-based nutrition education on caregivers’ KAP regarding complementary feeding at baseline, 3-month follow-up, and 6-month follow-up. In the absence of a gold standard test in the measurement of KAP, composite measures will be used in this study. A composite knowledge score will be built on 4 measures based on 4 self-report questionnaire items. Knowledge will first be estimated by each measure and classified into 2 categories as adequate and inadequate before the results of the 4 measures are finally combined into the composite knowledge score. Similarly, composite scores for attitude and practice will comprise 10 and 7 measures, respectively, as derived from corresponding numbers of self-report questionnaire items.

#### Secondary Objective

The secondary objective will be to compare nutrition outcomes of Mbororo children (aged 3-59 months) at baseline, 3-month follow-up, and 6-month follow-up in the control and experimental groups. Nutrition outcomes will be defined as child growth measured as length/height, weight, and weight-for-age at baseline and endline; and child morbidity status will be measured as self-reported incidence of diarrhea, fever, and cough at 2 weeks preceding baseline, and at 3-month and 6-month data collection.

### Outcome Measurements

#### Primary Outcomes

The primary outcomes will be caregivers’ nutrition-related knowledge, and attitudes and practices of caregivers as measured using self-reported items as shown in Table 1.

#### Secondary Outcomes

As shown in Table 1, the secondary outcomes will comprise child growth (height/length, weight, and weight-for-height), which will be measured at 6-month follow-up, and child morbidity status (diarrhea, fever, and cough 2 weeks preceding baseline), which will be self-reported.

**Table 1 table1:** Primary and secondary outcome variables among study participants at baseline, 3 months, and 6 months.

Outcome measures					Scale			Type			Measure			Analysis method

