**Results:**

Baseline data were collected in September 2019. In February 2020, 10 Mbororo communities (clusters) with 242 child–caregiver pairs were selected and allocated to the experimental and control arm in a 1:1 ratio. Community nutrition volunteers (n=6) and community health workers (n=6) were selected and trained. Data collection and analysis are ongoing, and results are not available for this manuscript.

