**Secondary Outcomes**														
	**Child growth at 3 and 6 months**													
		Weight	Ratio			Continuous			Change in weight			*t* test		
		Height/Length	Ratio			Continuous			Change in height/length			*t* test		
		Weight-for-height *z* score	Ratio			Continuous			Change in weight-for-height			ANOVA^a^		

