#### Anthropometric Measurements

Pretested portable anthropometry tools (battery-powered digital infant and toddler weighing scales, stadiometers, measuring tape, and lying wooden boards) will be used. The weight and height/length measurements will be performed using standard procedures [19]. Lying or sitting weights for children aged 0-23 months will be measured to the nearest 0.01 kg, and standing weights for older children will be measured to the nearest 0.1 kg. The weighing scale will be calibrated to 0 before each measurement. Recumbent lengths for children aged 0-23 months will be measured to the nearest 0.1 cm with measuring tape and lying boards placed on a flat ground surface. Standing heights for older children will be measured to the nearest 0.1 cm, with the head, shoulder, buttock, and heel touching the vertical surface of the stadiometer. Measurements will be taken twice and the mean recorded.

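### The child growth outcome is weight-for-age in two places and weight-for-height in two others, on conflicting schedules, and raw growth is tested without adjustment for age

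*Protocol article*

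**What the plan says.** Four places in the protocol article define the growth outcome.

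- **Abstract, Methods:** "child growth (weight, height/length, weight for age", with no separate timing for growth.
- **Secondary Objective:** the opening sentence compares nutrition outcomes "at baseline, 3-month follow-up, and 6-month follow-up in the control and experimental groups". The next sentence narrows growth to "child growth measured as length/height, weight, and weight-for-age at baseline and endline".
- **Secondary Outcomes text:** "child growth (height/length, weight, and weight-for-height), which will be measured at 6-month follow-up".
- **Table 1:** the block is labelled "Child growth at 3 and 6 months". Its three rows are change in weight (t test), change in height/length (t test) and a weight-for-height z score, with the measure given as "Change in weight-for-height" (ANOVA).

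Step 6 of the intervention section has both arms assessed at 3 and at 6 months with the baseline tools.

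The Data Analysis Plan repeats the t test and analysis of variance. It says nutrition outcomes are computed from anthropometric indices and set against the WHO 2006 median. It offers multivariate logistic regression on baseline variables as the adjusted analysis, promises intention-to-treat and says clustering will be considered.

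On dates, the abstract's Results state "Baseline data were collected in September 2019". Step 1 and the main Results section give August to September 2019, and selection and allocation are dated February 2020.

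**The concern.** Weight-for-age relates weight to age, and weight-for-height relates weight to stature. A short child of normal build can score low on the first and normally on the second, so an intervention effect on one need not appear on the other. With two indices and two visit sets in the same document, an analyst could report whichever combination looks better and cite the protocol for it.

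The second strand is efficiency. Expected gain in weight and length is much faster in infants than in four-year-olds. A t test on raw change leaves that variation in the error term. With only 10 clusters randomised, the arms may also differ in mean age by chance, and nothing in the stated analysis of these outcomes would correct for it.

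**Working it through.** **1. Index, side by side**

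| Place | Third growth measure | Test assigned |
|---|---|---|
| Abstract, Methods | weight-for-age | none specific to it |
| Secondary Objective | weight-for-age | none |
| Secondary Outcomes text | weight-for-height | refers to Table 1 |
| Table 1 | weight-for-height z score | ANOVA |

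The count is two against two. Weight-for-age is a named outcome with no row in Table 1. Weight-for-height has a row but does not appear in the objective.

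**2. Timing**

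The definition in the Secondary Objective (baseline and endline) and the Secondary Outcomes text (6-month follow-up) agree once endline is read as the 6-month visit and the measure as a change from baseline. Table 1 has 3 and 6 months, in line with Step 6 and with the opening sentence of the Secondary Objective. That makes two variants: endline only, or 3 and 6 months. They differ on whether growth at 3 months is an outcome.

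**3. Raw change without age adjustment**

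Inputs: 121 pairs per arm in 5 clusters (abstract) and ages 3 to 59 months (inclusion criteria). The share of variance in raw change explained by age, R², is not in the documents, so a range is assumed.

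Formulas: variance of the unadjusted comparison relative to the age-adjusted one = 1/(1 − R²). Effective children per arm = 121 × (1 − R²).

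| R² (assumed) | Variance ratio | Effective children per arm |
|---|---|---|
| 0.10 | 1.11 | 108.9 |
| 0.20 | 1.25 | 96.8 |
| 0.30 | 1.43 | 84.7 |
| 0.50 | 2.00 | 60.5 |

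These figures are before any design effect for clustering. The logistic model in the Data Analysis Plan takes a binary outcome, so it cannot recover this loss for change in kilograms or centimetres.

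**4. Length of the interval**

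The documents date baseline and allocation but not the first session or any follow-up visit. If follow-up runs from allocation (assumption), the 6-month visit falls at February 2020 + 6 months = August 2020. From September 2019 that is 11 months; from August 2019 it is 12. If six months were counted from the September baseline, endline would be March 2020, one month after allocation. That cannot hold the six months of fortnightly sessions described in Step 4. The change from baseline therefore probably spans more than 6 months.

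**The case against.** The best defence is that Table 1 governs. The Secondary Outcomes text points to it, its caption lists baseline, 3 and 6 months, and this fits Step 6. That makes a schedule of 3 and 6 months the more plausible intention. It does not remove the endline-only wording in two other places, and it leaves weight-for-age, named in both the abstract and the objective, without an analysis.

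It can also be said that analysis detail belongs in a separate plan. That would cover an omission. Here the article states the definition more than once, and differently.

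On raw change, the defence is largely right. Randomisation makes the comparison valid on average, and the plan promises to consider clustering. What remains is lost precision and exposure to chance imbalance.

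A reader might infer more than the documents support:

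- **No standardised score is used.** Table 1 has one z score, standardised to height rather than age, and the Data Analysis Plan mentions the WHO 2006 standard without naming an index or a between-arm test. The remark about raw change applies to two of the three rows.
- **The change from recumbent length to standing height biases the result.** Anthropometric Measurements begins its length rule with "Recumbent lengths for children aged 0-23 months" and uses standing height for older children, by the same age rule in both arms. No difference between arms follows.
- **Children who pass 60 months must be left out.** The article gives no upper age for the WHO comparison, and dropping randomised children would conflict with the intention-to-treat statement.

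**Conclusion.** The inconsistency of index and timing stands on the text alone and needs no assumption. It concerns secondary outcomes, and it should be corrected.

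The raw-change point is a precision remark. Under the assumed R² of 0.10 to 0.50, the unadjusted test gives up the equivalent of about 12 to 60 of 121 children per arm (121 − 108.9 = 12.1; 121 − 60.5 = 60.5), before clustering. The documents give neither R² nor a standard deviation, so the true loss is unknown. It would be wrong to call the comparison biased: a difference in mean age between arms would be a chance event under randomisation, although with 5 clusters per arm not a remote one.

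The interval of about 11 months is likely but conditional on follow-up being counted from allocation.

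**What to change.** Before the arms are compared (the Results section says data collection and analysis are still under way):

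1. Bring the abstract, Secondary Objective, Secondary Outcomes text and Table 1 to one set of indices and one visit schedule, and give every named index its own analysis row.
2. Analyse growth either as age- and sex-standardised scores or as raw values adjusted for age and sex. In both cases include the baseline value as covariate, use age at the actual visit, and apply the clustering allowance already promised. Use a model for continuous outcomes rather than the logistic one.
3. Report the actual time from baseline to each follow-up visit, by arm, and describe the change by that interval.
4. Keep all randomised children in the analysis, in line with intention-to-treat.

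The cost is wording and a little programming. Weight and height/length are already measured, and child demographics are in the questionnaire (assumed to include age and sex). No new measurement is needed if anthropometry is taken at 3 months, as Step 6 implies; if it is not, the reconciled schedule should say endline only.
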